### Muscle strength test - maximal voluntary isometric contraction (MVIC)

Knee maximal voluntary isometric contraction (MVIC) extension and flexion will be measured using a *handheld* dynamometer (Lafayette Instruments, Lafayette, IN, USA). Prior to the tests to measure the MVIC, participants will be positioned and asked to perform sub-maximal contractions for warm-up and familiarization with the test. Quadriceps MVIC will be performed in the seated position with a hip angle of 90° flexion and knee angle of 0° (full extension). A Velcro strap (attached to the floor) will be wrapped around the ankle, and another strap will be used to maintain the pelvis against the table. Evaluation of the knee flexor MVIC will be performed at 15° knee flexion in the supine position. A Velcro strap will be wrapped around the ankle and another to secure the pelvis against the table.

The tester will place the dynamometer at the front of the ankle under the Velcro strap to measure knee extension force, and at the back of the ankle under the Velcro strap to measure knee flexion force. Before each test, the tester will demonstrate the direction of the force required. The participant will be instructed to contract “as forcefully as possible”, with a gradual increase in force and strong verbal encouragement will be provided during the contractions. The tester will maintain the dynamometer stable, to prevent it from being displaced. The participants will perform 3 MVIC separated by a 60-s pause (Selistre et al. 2017), and the highest value will be used for analysis. The MVIC will be expressed in kgf [73]. The reliability of the isometric muscle tests with a handheld dynamometer has been reported previously. Studies demonstrated excellent concurrent validity compared with an isokinetic dynamometer and also excellent inter-tester and intra-tester reliabilities for measuring maximal isometric strength in the main movements of lower limbs [74–77]. Additionally, in a pilot study with 10 participants with the same sample characteristics, a two-way mixed model was used to calculate the intraclass correlation coefficient (ICC) within trials. The average measure with 95% confidence interval (CI) and coefficient of variation (CV) were calculated in order to demonstrate the reliability of the mean of recordings. The ICC values of MVIC were higher than 0.80, ranging from 0.88 to 0.98. The CV values ranged from 11 to 32%.

### Muscle quality

Muscle quality is the intrinsic ability of muscle tissue to produce force, which will be estimated through the ratio between the muscle strength, obtained by MVIC, and lean mass of the thigh, obtained by computed tomography (kgf/cm^2^) [78].

### Periodized circuit training protocol (CT)

#### Selected exercises

For elaboration of the periodized circuit training protocol, specific exercises for the knee OA population were selected from previously published studies [79–81].

These exercises were previously arranged in a circuit model: upper body (UB), lower body (LB), and trunk and global exercises (which involve the whole body). A total of 47 exercises were selected (Additional file 1) and then stratified in a pilot study according to the stress intensity levels; light, moderate, and intense. For the stratification, all exercises were performed by 10 subjects with similar characteristics to this study sample (age, demographics, and clinical condition). All participants in the pilot study used a heart rate monitor (Polar V800, Polar Electro Oy, Finland) to obtain HR and the Rating of Perceived Exertion (RPE) was evaluated through the Borg scale with 6–20 points, before and immediately after each exercise. Subsequently, the percentage of the maximum heart rate (%HRmax) was calculated, by subtracting 220 from the participant’s age [82]. For stratification, the Muyor (2013) study was considered, with Rating of Perceived Exertion (RPE) values 6–10: mild; 11–14 moderate; 15–20 intense; and ​​%HRmax values: < 54% light; 55–69% moderate; > 70% intense [82].

The 47 exercises selected were divided into three days (20 per day), with a 48-h interval between them. The participants were instructed to perform each exercise for 30 s, as fast as possible, and a rest interval was given between exercises, considered sufficient for HR to return to pre-exercise values. The interval time ranged from 1 to 3 min. Therefore, with the results of the pilot study, it was possible to organize these exercises through the 14-week training protocol, respecting the intensity progression (light, moderate, and intense).

During the training protocol, it was determined that the exercises stratified as mild will last 20 s, moderate exercises will last 30 s, and the intense exercises for 40 s. Between each station, as described above, there will be a maximum of 30 s rest. This strategy will be used to require the contraction of several muscle groups, with a short rest between stations, causing cardiovascular and metabolic benefits and greater reduction in adipose tissue [83]. It should also be noted that this technique, in addition to resulting in a lower total exercise time, maximizes the impact of an exercise protocol in a short time.

#### Application of the periodized circuit training protocol

The circuit training protocol will be conducted in three sessions per week for 14 weeks, totaling 42 exercise sessions. The minimum percentage of sessions that the participants is required to attend is 75% of the total sessions. Each session will consist of: warm-up exercises for 5 min, CT, and cool-down for 5 min with global stretching exercises. Initially, participants will be asked for their perception of pain or discomfort through a visual analogue scale (VAS) and will be instructed to inform the location of the pain through the Nordic questionnaire musculoskeletal symptoms; baseline blood pressure (BPi) and initial heart rate (HRi) will also be measured. Subsequently, the participants will perform a warm-up exercise for 5 min on a stationary bicycle with minimum resistance.

Immediately after the warm-up exercise, each participant will perform the circuit training protocol. The participants will be instructed to perform each exercise as fast as possible, with the maximum number of repetitions during the established time in each training phase (light, moderate, and intense). The first station of exercises to be performed will be defined in a random order at each session. After the end of the first exercise station, the participant will move to the next exercise station, following a specific order to allow different muscle groups to alternate between rest and work, favoring recovery and minimizing the risk of muscle fatigue [34] as shown in Fig. 2.

**Fig. 2 Fig2:**
[figure not shown]
Circuit training protocol - Station organization

Periodized dynamic intensity is a strategy used to define the dynamic intensity according to weeks of training (Fig. 3). The volume of work is defined by the training session duration and through the previously stratified intensity of effort and heart rate response to exercise, as described above.

**Fig. 3 Fig3:**
[figure not shown]
Periodized dynamic loads of the circuit training protocol

The construction of the periodization model to be used, regarding the biological principle of volume vs. intensity interdependence, and a duration of 14 weeks, proposes a week of recuperative exercises after two weeks of stress, gradually increasing the intensity with respective volume settings. This model is based on the concepts described by Turner (2011) which concludes in favor of the organization of training adapted to the reality of the public to be trained.

The representation in Fig. 3 can be detailed as follows: the yellow column represents the adaptation and familiarization week (1st week) in which participants will be familiarized with the materials and exercises performed during the training. The exercises previously stratified as light will be performed in the second, third, and fifth weeks of training (green columns), moderate exercises will be performed in the sixth, eighth, and ninth weeks (purple columns), and intense exercises will be performed in the eleventh, twelfth, and fourteenth weeks (red columns).

The blue columns represent regenerative weeks in which the training will be performed at light intensity, but in this case, each exercise will have a 10 s duration with an increase of 10 s in the recovery time of each station, accounting for a smaller workload with mild exercise.

The exercise intensity will be increased at the 6th and 11th weeks, as shown in Fig. 3. This will be based on the pilot study performed, as described.

It is possible to observe that from the second week, the protocol follows a progression method based on the intensity of effort and the volume of work (time). Three points must be observed in this model: i-) the three intensities, according to the proposed classification, are carried out for three weeks each; ii) every two weeks of training, with intensities that aim at adaptation through stress, there is a recovery week (increase of metabolism with less structural and cardiovascular impact) and; iii) the two weeks between the recoveries are composed of implementation in the workload or in the effort intensity.

Thus, the planning progresses in a nonlinear manner. Changes in volume and intensity offer new challenges every week and show how it becomes increasingly easy to perform lower-intensity exercise. The principle of adaptation suggests stress and recovery to achieve goals and this was the intention in setting up this routine: To cause a controlled stress (stratification already described), to increment such stress, (either in the workload or the intensity of the effort) and to alternate periods of increment and recovery to stimulate the perception of adaptation acquired by participants [84].

Immediately after each training session, RPE; Final blood pressure (BPf); final heart rate (HRf); and VAS will be measured again.

### Strength training protocol

Strength training is one of the most common types of exercise prescribed for the knee OA population, and in general has shown beneficial results on various parameters. For this reason, the strength training protocol used in this study will follow the model proposed by Selistre et al. (2017) with minor modifications. This protocol demonstrated reduced muscle weakness, pain, and disability in men with early knee osteoarthritis [81]. Each session will have an average duration of 60 min, with three sessions per week for 14 weeks, also totaling 42 exercise sessions. The same exercises as performed in the circuit training protocol were selected for the lower body and trunk. The strength training will also include the same warm-up (five minutes of stationary bicycle) and cool-down strategies (5 min global stretching).

Table 1 shows the exercise distribution during the 14-week strength training protocol. The strength training protocol is divided into three levels. In the first level (1st-5th weeks), three quadriceps strengthening exercises and one strengthening exercise for the hamstrings, hip abductors, and adductors will be performed. In the second level (6th–9th weeks), three quadriceps strengthening exercises and strengthening exercise for the hamstrings, hip abductors, and adductors, and three trunk exercises will be performed. In the third level (11th–14th weeks), the same exercises as in the second level will be performed, but with higher difficulty.

**Table 1 Tab1:** 14-week Strength Training Protocol exercise distribution

Level/Weeks	Exercise
Level 1 - 1st to 5th weeks	Semi squats (50°)^a^
	Knee extensor strengthening with ankle weights.^a^
	Straight leg raises with ankle weights.^a^
	Hip abductor strengthening with ankle weights.^a^
	Hip adductor strengthening with ankle weights.^a^
	Knee flexor strengthening with ankle weights.^a^
Level 2 - 6th to 9th weeks	Level1
	Traditional bridge^a^
	Knee plank^b^
	Side knee plank^b^
Level 3 – 10th to 14th weeks	Level1
	Plank^b^
	Side plank^b^
	Bridge on bosu^b^

^a^ = *2 × 15 rep; 1 min between sets;*^b^ *= 3 × 10 seconds*

The initial load set for each exercise will be based on the one repetition maximum test (1 RM). Strengthening exercises will be performed in two sets of 15 repetitions, using 25% 1RM for hip adductors and abductors, and 50% 1RM for the quadriceps and hamstrings, using ankle weights. Ankle weights will be progressed if necessary. During knee extensor and flexor, and hip adductors and abductors strengthening, participants will perform each repetition with a 5 s isometric muscle contraction. Exercises for the trunk will be performed in three 10-s series, increasing the duration when participants are able.

### Educational protocol

The educational protocol will follow the model proposed by Messier et al. (2013b), in order to provide care, social interaction, and health education [2]. Meetings of 60 min will be held twice a month for 14 weeks, totaling 8 meetings. Interactive presentations will be performed addressing topics such as pathophysiology of osteoarthritis, and American College of Rheumatology (ACR) recommendations on nutrition, posture, and lifestyle. In addition, at the end of the meetings, participants will perform the same stretching exercise as performed in the exercised intervention protocols, but only on the upper body for five minutes, in order to improve adherence and increase the perceived benefits. According to the authors, there is no evidence that this practice of health education can directly influence the primary results of the present study [2]. Participants in the trained groups will also participate in the education and health sessions at separate times.

### Statistical analysis

Data analysis will be performed using the software *Statistical Package for the Social Sciences* version 20.0 (*SPSS* Inc., Chicago, IL, USA). An intention to treat analysis will be conducted for all data analyses. Initially, descriptive analysis of variables will be performed as mean, standard deviation, and coefficient of variation. Next, normality and homogeneity of variance will be checked by the Kolmogorov-Smirnov test and Levene’s test, respectively**.** If normal distribution of data is not observed, the same transformations will be carried out, to allow the application of parametric tests**.**

Two-way ANOVA (group X time) will be conducted for the dependent variables. When significant differences were observed in the group or interaction, will be performed a post-hoc Bonferroni Test. For all measured variables, the estimated sphericity will be examined in accordance with Mauchly’s W Test, and the Greenhouse-Geisser correction will be used as needed. For comparison between moments, for uCTX-II, sCOMP, and MVIC repeated measures ANOVA (baseline X during protocols X follow-up) will be performed. When significant main effects are found, the Bonferroni test will be used to identify statistical differences. For IL1-β, IL-6, TNF-α, leptin, adiponectin, WOMAC, PCS, DXA, computed tomography, and functional performance-based tests, the t-test will be used (baseline X follow-up). For all analyzes a significance level of 5% will be adopted (*p* < 0.05). No interim efficacy or subgroup analyses are planned.

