**Methods:**

This study presents a protocol for a randomized controlled trial. Sixty selected participants diagnosed with knee OA grades II and III, 40–65 years old and BMI < 30 kg/m^2,^ will be randomly divided into three groups:periodized circuit training, strength training, and educational protocol. The circuit training and strength training protocols consist of 14-week training protocols conducted 3 times a week. The circuit training group will perform selected exercises previously stratified as light, moderate, and intense, arranged progressively in a circuit model, the strength group will perform regular strength exercises, and the educational protocol group will participate in a 14-week protocol with lectures twice a month about healthy lifestyles. Baseline and follow-up evaluations will be conducted for thigh interMAT (computed tomography), body composition (DXA), inflammation (IL-1β, IL-6, IL-10, TNF-α, leptin, and adiponectin), and joint degradation biomarkers (uCTX-II and sCOMP), performance-based tests (30s Chair Stand Test, 40 m Fast-paced Walk Test and Stair Climb Test), quadriceps and hamstring maximal isometric voluntary contraction (MIVC), and questionnaires (WOMAC and pain catastrophizing scale). Repeated measures ANOVA will be used to compare differences between groups (circuit training X strength training X educational protocol) at the different times of assessment (baseline x follow-up or baseline x during protocol x follow-up) for each of the dependent variables. When significant main effects were found, the pots hoc Bonferroni test will be used to identify statistical differences. A significance level of 5% (*p* < 0.05) will be adopted.

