### Sample

To determine the sample size, the data of thigh interMAT from the study of Griessmann et al. (2014) were considered [55]. 16 participants per group was stipulated through a two-tailed hypothesis test, with a 5% level of significance and 80% test power.

Considering the possible sample loss in the course of the study, 20 subjects each, totaling 60 participants of either sex will be included in this study.

To be eligible, participants will be required to fulfill the following criteria:i.Aged between 40 and 65 years;ii.KOA clinically diagnosed fulfilling the American College of Rheumatology classification criteria of knee pain on most days of the past month and radiographically, classified as grades 2 or 3 according to Kellgren and Lawrence criteria [56].iii.Knee pain for ≥3 months;iv.Overall average knee pain in the last week ≥4 on a 0 to 10 Visual Analogue Scale (VAS).

The exclusion criteria are:i.Knee surgery;ii.Body mass index (BMI) ≥30 kg/m^2^;iii.Previous history of lower limb trauma;iv.Physical therapy, chiropractic, or acupuncture treatment or exercises specifically for the knee within the previous 6 months;v.Walking more than 30 min continuously daily or participating in a regular (more than twice a week) exercise program;vi.Current or past (within 3 months) oral or intra-articular corticosteroid use;vii.Systemic arthritic conditions such as rheumatoid arthritis;viii.Inability to walk unaided as this is necessary for some of the physical testing;ix.Medical condition precluding safe exercise such as uncontrolled hypertension, heart condition, cardiac pacemaker use, chronic diseases, impaired renal function, or any other medical condition that precludes participation in the study [57, 58];x.History of severe muscular lesions (above grade I);xi.Motor impairment due to neuromuscular diseases;xii.Cognitive deficits that compromise understanding of the tests;xiii.Starting any other exercise protocol or physical therapy during the study.xiv.Unable to comply with the protocol such as inability to attend therapy session or attend assessment appointment at the University.xv.Kellgren and Lawrence grades 0, 1, and 4.

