Data collections will be performed over the 14 weeks of the study. At baseline and post 14 weeks intervention (follow up) the following will be performed: computed tomography of thighs, maximal voluntary isometric contraction (MVIC), performance-based tests, blood and urine samples, questionnaires, and DXA. In the 5th, 10th, and 14th weeks, blood and urine samples will be collected for sCOMP and uCTX-II analysis and the MVIC test will be conducted.

All analyzes will be performed for all groups blindly, i.e., the evaluator of the collected data will be blinded to the group allocation.

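### Intention-to-treat is promised for every analysis, but the named ANOVA and t-tests use complete cases only and no stated step keeps randomised participants with missing follow-up

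*Protocol article*

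**What the plan says.** All of the following is in the protocol article.

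- **Population** (Statistical analysis): "An intention to treat analysis will be conducted for all data analyses".
- **Between-group method** (Statistical analysis): "Two-way ANOVA (group X time) will be conducted for the dependent variables", with Mauchly's test and the Greenhouse-Geisser correction. The abstract confirms the type of ANOVA: "Repeated measures ANOVA will be used to compare differences between groups".
- **Change over time, several visits** (Statistical analysis): "for uCTX-II, sCOMP, and MVIC repeated measures ANOVA (baseline X during protocols X follow-up) will be performed".
- **Change over time, two visits** (Statistical analysis): for the cytokines and adipokines listed, the questionnaires, DXA, "computed tomography, and functional performance-based tests, the t-test will be used (baseline X follow-up"). This list includes the CT measurement that supplies the primary outcome. The word paired is not used but is implied.
- **Visits** (Procedures): "In the 5th, 10th, and 14th weeks, blood and urine samples will be collected for sCOMP and uCTX-II analysis", and MVIC is tested at the same weeks. CT, DXA, questionnaires and performance tests are done at baseline and week 14 only. Randomisation follows the baseline evaluations.
- **Expected loss** (Sample): 16 per group are needed. Then: "Considering the possible sample loss in the course of the study, 20 subjects each, totaling 60 participants of either sex". No dropout rate is given.

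**The concern.** The declared population and the named tests do not fit together. Classical repeated-measures ANOVA needs a complete row of values for each participant, and a baseline-to-follow-up t-test needs both values. Anyone lost before week 14 therefore leaves the analysis of the primary outcome, although that person was randomised and the plan says everyone is analysed. The ANOVA cannot easily be read as an ordinary one that treats visits as independent. The sphericity checks apply only to repeated measures, and the abstract uses that name.

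What is at stake is mainly bias. The two exercise arms are asked to attend 42 sessions each, and the education arm 8 meetings. Participants enter with knee pain of at least 4 out of 10, and the Discussion itself ties attendance to perceived benefit. Dropout could therefore differ between arms and be related to response. The comparison among completers is then no longer protected by randomisation. Data already collected from participants with one missing visit are also thrown away.

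**Working it through.** **Inputs from the article**

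- Needed: 16 per group, two-sided 5%, 80% power (Sample).
- Enrolled: 20 per group, 60 in total (Sample).
- Visits: baseline and week 14 for interMAT and most outcomes; baseline and weeks 5, 10 and 14 for uCTX-II, sCOMP and MVIC (Procedures).

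**Assumptions, because the article gives no figure**

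- Loss before week 14: *d* = 5% to 30%.
- Missed interim visits among those who stay: *m* = 5% to 10% at each of weeks 5 and 10, independently.

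**Step 1: the plan's own figure.** The implied loss is 1 − 16/20 = 0.20, and 16 / (1 − 0.20) = 20 per group, so 60 in total. This agrees with the article, but 20% is back-calculated, not stated. The 16 itself cannot be reproduced, because no difference or SD is given.

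**Step 2: two-visit outcomes, including interMAT.** Randomisation comes after baseline, so in essence only week 14 can be missing. Complete cases = 60 × (1 − *d*):

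| Loss *d* | 5% | 10% | 15% | 20% | 25% | 30% |
|---|---|---|---|---|---|---|
| Analysed | 57 | 54 | 51 | 48 | 45 | 42 |

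**Step 3: four-visit outcomes.** Loss by week 14 is already in *d*, so only the two interim visits add to it. Complete cases = 60 × (1 − *d*) × (1 − *m*)²:

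| Loss *d* | *m* = 5% | *m* = 10% |
|---|---|---|
| 10% | 60 × 0.90 × 0.9025 = 48.7 | 60 × 0.90 × 0.81 = 43.7 |
| 20% | 60 × 0.80 × 0.9025 = 43.3 | 60 × 0.80 × 0.81 = 38.9 |

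At 20% loss, 48 − 43.3 = 4.7 and 48 − 38.9 = 9.1. About 5 to 9 participants with both a baseline and a week-14 value would thus be discarded only because an interim sample or test was missed.

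**Step 4: power.** Assume that the 16 refers to a comparison of two groups. The standardised difference giving 80% power at 16 per group is then 1.02 (noncentral t). With that difference, power is about 88% at 20 per group, 80% at 16 and 74% at 14 (the last corresponds to 42 in total). Losing the whole allowance equally across arms still leaves the planned power.

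**The case against.** The strongest reply is that this is silence rather than error. The section states the principle and names the tests. It nowhere says that incomplete participants are excluded, and the 75% attendance requirement in the circuit-training section carries no stated consequence for the analysis. Imputation before the ANOVA, or complete follow-up of those who stop, would be compatible with every sentence, and an article may leave such detail to a fuller document. This stands to the extent that a complete-case result is not certain. It does not remove the point, because the article fixes specific tests, and applying those tests as written gives a complete-case result under an intention-to-treat label.

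The documents do not support several stronger readings that a reader might infer:

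- **That the plan forecasts a 20% loss, so that 48 or fewer will be analysed.** Four per arm is an allowance. 48 is what remains if all of it is used, and smaller losses leave more.
- **That any missed visit removes a participant from everything.** A missed week 5 or 10 affects only uCTX-II, sCOMP and MVIC.
- **That the four-visit outcomes fall to 41 or 35.** Those numbers come from 60 × 0.80 × 0.95³ and 60 × 0.80 × 0.90³, which apply missingness at week 14 on top of the dropout already counted there.
- **That the trial becomes underpowered.** At 48 it is not.
- **That a mixed model cures the problem for interMAT.** A dropout contributes a baseline scan but no observed change, and the model assumes data missing at random.

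Differential, response-related dropout is plausible from the design, but no figure in the article establishes it.

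**Conclusion.** The concern holds as an inconsistency between the promised population and the named methods, and it reaches the primary outcome. How many participants leave the analysis depends on losses the article does not quantify: 12 of 60 for interMAT if the whole allowance is lost (60 − 48), and about 17 to 21 of 60 for the four-visit outcomes under the further assumption of 5% to 10% missing at each interim visit (60 − 43 and 60 − 39). The consequence is possible bias, wasted partial data and a label the tests do not earn, not a shortfall against the planned power. It should be fixed. It is not fatal to the design, since imputation or complete follow-up could still honour the promise.

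**What to change.** **Analysis.** Replace the repeated-measures ANOVA and the t-tests with a linear mixed model, using the MIXED procedure of the SPSS package already named. Include all randomised participants in their assigned group, all available time points, an unstructured covariance and baseline means constrained equal across arms. Take the between-arm differences at week 14, and the changes over time, as contrasts from this model. The Mauchly and Greenhouse-Geisser steps are then no longer needed.

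**Follow-up.** State that week-14 assessments will be sought from participants who stop training or attending.

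**Sensitivity.** Add one analysis for interMAT that allows dropout to be non-random, for example by shifting the unobserved week-14 values over a stated range, separately by arm.

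Settle this before the group allocation is revealed to the statistician, so that the handling of dropouts cannot be guided by the results.

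**Cost.** A change of wording, modest extra analysis work, effort to bring back those who stop, and reliance on missing at random in the main model. For the four-visit outcomes the gain is direct, because partial records are used. For the two-visit outcomes the model adds only the dropouts' baseline values, so the week-14 follow-up and the sensitivity analysis matter most there.

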## Methods/Design

### Aim

The main objective of the present study will be to compare the influence of 14-weeks of periodized circuit training with strength training and an educational protocol on thigh interMAT and body composition. Secondarily, the present study will investigate these effects on indicators of cartilage degradation and systemic inflammation, and its repercussions on physical function, pain, and quality of life in patients with knee OA.

Our general hypothesis is that both circuit training and strength training protocols will promote decreases in thigh interMAT, associated with improvement in body composition and muscle strength, and a reduction in inflammatory cytokine concentration (IL1β, IL6, TNF-α), pain, and stiffness in patients with knee OA, leading to consequent improvement in quality of life, compared to the educational protocol. However, it is hypothesized that these benefits, mainly related to the improvement in the body composition and reduction in interMAT will be more evident after the circuit training, compared to the strength training. Additionally, it is also hypothesized that biomarkers of joint degradation may signal exercise efficiency for both groups over the application of both training protocols.

The following methodology is in full agreement with the SPIRIT (Standard Protocol Items for Randomized Trials) recommendations [50–52] [50–52] and the Osteoarthritis Research Society International (OARSI) recommendations for RCTs [53] to ensure methodological rigor. Consolidated Standards of Reporting Trials (CONSORT) [54] guidelines will be followed for reporting the results in a subsequent article.

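### Baseline-to-follow-up tests run at 5% beside the group-by-time ANOVA with no stated precedence, so the primary outcome has two tests and only one of them compares the randomised arms

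*Protocol article*

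**What the plan says.** The Statistical analysis section begins with an analysis that compares arms: "Two-way ANOVA (group X time) will be conducted for the dependent variables". No outcome is excluded. The follow-on rule is: "When significant differences were observed in the group or interaction, will be performed a post-hoc Bonferroni Test".

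Two sets of tests over time follow.
- For the outcomes also measured during the programme: "For comparison between moments, for uCTX-II, sCOMP, and MVIC repeated measures ANOVA (baseline X during protocols X follow-up) will be performed".
- For the listed cytokines and adipokines, WOMAC, PCS, DXA, CT and the performance tests, a t-test of baseline against follow-up: "DXA, computed tomography, and functional performance-based tests, the t-test will be used (baseline X follow-up").

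A single 5% level is set for all analyses. Under Thigh computed tomography, interMAT is named as the primary outcome, so the t-test sentence covers it.

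The Methods part of the Abstract supports the between-arm reading: "Repeated measures ANOVA will be used to compare differences between groups (circuit training X strength training X educational protocol"), at the times "baseline x follow-up or baseline x during protocol x follow-up) for each of the dependent variables". It ties post hoc testing to main effects and does not mention the interaction.

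The Aim section compares three arms and expects that the benefits "will be more evident after the circuit training, compared to the strength training".

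**The concern.** A t-test of baseline against follow-up asks whether an outcome moved over time. It does not ask whether one randomised arm moved more than another. The protocol gives the primary outcome both kinds of test at the same level and does not say which one decides. It neither makes the time test conditional on the interaction nor calls it descriptive.

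The Aim's wording makes this matter. A significant change after circuit training beside a non-significant change after strength training or education could be reported as support for the hypothesis, and no sentence in the plan prevents it. That pattern is weak evidence of a difference between arms.

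The post hoc trigger has a related flaw. A significant group main effect is enough to open the arm comparisons. In a baseline-and-follow-up layout that effect is an average over both times, so it is not the treatment effect.

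**Working it through.** **Inputs from the protocol (Sample; Statistical analysis).** Three arms; 16 per arm after losses and 20 enrolled; two-sided 5%. No effect size or SD is given, so the figure of 16 cannot be reproduced. By n = 2(1.96 + 0.842)²/d² = 15.7/d², it fits a standardised difference d of about 1.0. Only the arm size is used below.

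**Assumed inputs.** The same true change in every arm, independent arms, normal data and time tests run within each arm. Change is in units of the baseline SD, with correlation r between baseline and follow-up.

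**Step 1: power of one within-arm test.** The SD of change is √(2(1 − r)). With r = 0.8 this is √0.4 = 0.632. A change of 0.3 SD is then 0.3/0.632 = 0.474 SDs of change. The paired t-test with n = 16 has power p = 0.427 (noncentral t).

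**Step 2: disagreement between arms that do not differ.**
- Three arms not all on the same side of p < 0.05: 1 − p³ − (1 − p)³ = 1 − 0.078 − 0.188 = 0.734, or about 73%.
- Circuit significant and education not: p(1 − p) = 0.427 × 0.573 = 0.245, about a quarter.

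**Step 3: range over the assumptions.**

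| Setting, equal true change in all arms | n = 16 | n = 20 |
|---|---|---|
| No change in any arm | 14% | 14% |
| 0.3 SD, r = 0.8 | 73% | 75% |
| Change 0.2 to 0.5 SD, r 0.5 to 0.8 | 31% to 75% | 23% to 75% |
| Change of 1.0 SD of change | 11% | 3% |

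The no-change row is 1 − 0.05³ − 0.95³ = 0.143.

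**Step 4: the planned between-arm test.** With two time points, the group-by-time interaction is a one-way F test on change scores. In 40,000 simulated trials per setting with equal true change, it rejected in about 5% at both arm sizes.

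**Step 5: the group main effect.** Let two arms differ by b at baseline and by b + δ at follow-up.
- Main-effect contrast: (b + b + δ)/2 = b + δ/2. It halves the effect and keeps any chance baseline difference.
- Interaction contrast: (b + δ) − b = δ.

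With unit SD at both times and r = 0.8, the average has SD √((1 + 0.8)/2) = 0.949 and the change has SD 0.632. With b = 0 the standardised signals are 0.5δ/0.949 = 0.53δ and δ/0.632 = 1.58δ. The main effect carries one third of the interaction's signal.

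**The case against.** The strongest reply is that the plan already contains the right analysis. The group-by-time ANOVA comes first and excludes no outcome. The Abstract confirms a three-arm comparison for every dependent variable, including those measured only twice. The tests over time are introduced as comparisons between time points, and nothing says that arms will be compared by which of them reaches p < 0.05. This stands. A reader might infer that the t-test is the only test for interMAT, or that the trial ignores its randomisation; the documents do not support either inference.

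Three further points also stand.
- The protocol does not say that the t-tests are run within arms. That is the natural reading, and the disagreement figures depend on it. A test pooled over arms would not compare arms either.
- The 73% describes a misreading of the results. It arises only if time tests are set against each other in place of the interaction.
- A reader might add regression to the mean, because entry requires "Overall average knee pain in the last week ≥4 on a 0 to 10 Visual Analogue Scale (VAS"). That score is an entry criterion and is not among the outcomes in the t-test sentence, where pain is measured by WOMAC. No entry threshold is set on interMAT. The argument therefore gives no usable size for the listed outcomes.

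It may also be said that test hierarchy belongs in an analysis plan that is not shown. That answers less. The protocol itself names these tests, gives them the 5% level and sets the post hoc trigger, so the question is what it has fixed rather than what it has left out.

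**Conclusion.** The point holds in a limited form. The randomised comparison is planned. What is wrong is that the primary outcome and most secondary outcomes also carry a 5% test that does not compare arms, with no order of precedence, and that a group main effect may open the post hoc comparisons.

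The size is conditional. If within-arm tests are set against each other, arms with an identical true change disagree on significance in about 73% of trials in the illustrative case, and in 31% to 75% over the assumed range at 16 per arm. The interaction rejects falsely in about 5%. Change, correlation, normality and independence of arms are assumptions, since the protocol gives no SD or effect size. The figures show what the plan leaves possible and do not predict what the investigators will report.

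The logical point needs none of these assumptions: a baseline-to-follow-up test cannot establish that benefit is greater in one arm than in another. Because this touches the primary outcome and the central comparative claim, it should be settled before analysis.

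**What to change.** Amend the Statistical analysis section, and align the Abstract, as follows.

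1. State that the group-by-time interaction, or the between-arm difference in follow-up or change with its 95% CI, decides interMAT and every efficacy claim.
2. Open post hoc arm contrasts on the interaction only, and remove the group main effect as a trigger.
3. Replace the baseline-to-follow-up t-tests, and any time-only significance test for uCTX-II, sCOMP and MVIC, with within-arm mean change and 95% CI, labelled descriptive.
4. Keep the multi-visit model for uCTX-II, sCOMP and MVIC and state that it includes group, time and their interaction. Deleting that sentence outright could remove the section's only explicit mention of the visits during the programme.

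The cost is a few sentences. No extra data, visits or participants are needed.
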